### Randomization

2.4

Suitable participants, who agree to participate in this RCT, will be randomly assigned to a UCHA group or a placebo group at a 1:1 ratio. A total of 164 eligible participants each will be allocated to the UCHA and placebo groups. An internet-based research randomizer (IRR) developed by the contract research organization (CRO), the Institute of Safety and Effectiveness Evaluation for Korean Medicine (ISEE), will perform the assignment. A random order will be generated by the CRO's independent professional statistician using the R software (The R Foundation for Statistical Computing, Vienna, Austria) and stratified by the hospital using random block sizes of 2 and 4 based on the allocation code provided by the R software.

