##### ST: Thermometer measurement

2.8.2.1

After 20 minutes of relaxation at 24 ± 2°C, the ST will be measured by a thermometer (Testo 835-T1, Lenzkirch, Germany) at acupoints PC8, LU4, ST32, and LR3 at visit 2, 3, 4, and follow-up.

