##### World Health Organization Quality Of Life Scale Abbreviated Version (WHOQOL-BREF)

2.8.2.2

The Korean version of the WHOQOL-BREF consists of a 26-item questionnaire that measures 5 domains of an individual's quality of life, namely general quality of life; psychological, physical, and environmental health; and social relationships.^[15]^ It will be conducted at visits 2, 4, and follow-up.

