##### Efficacy assessment

2.8.7.1

For the efficacy assessment of this trial, both ITT and per-protocol (PP) analyses will be performed. Missing data will be adjusted using the last-observation-carried-forward (LOCF) imputation method on ITT analysis. The continuous variables will be expressed as the mean ± SD and the nominal variables will be reported as percentages. The ITT method will include all randomized subjects, regardless of any protocol violations or trial dropouts. The PP method will include only the subjects who have completed the whole study period without any major protocol violations and who have medication compliance rate equal to or greater than 70%. Missing values from the efficacy analysis will be modulated by applying the LOCF. The baseline demographic information will be compared by either a chi-square test for nominal variables or an analysis of variance (ANOVA) for continuous variables. For the within-group analysis, the primary and secondary outcome variables will be assessed using a paired *t* test. The between-groups analysis after 8 weeks of administration will be performed using a repeated-measure ANOVA for the primary outcome variables, and a paired *t* test for the mean difference in the VAS score between the SDT and placebo groups. As a secondary outcome variable, the mean differences in ST and WHOQOL-BREF scores between the groups will be analyzed using a repeated-measure ANOVA for ST and an ANOVA and post-hoc analysis for the WHOQOL-BREF scores. For all non-normal distribution data, a nonparametric statistical test will be performed. SPSS for Windows version 25.0 (SPSS Inc., Chicago, IL) will be used for statistical analysis. The statistical significance level will be set at *P* < .05.

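### The WHOQOL-BREF test, an ordinary ANOVA with post-hoc analysis, does not fit two arms and three visits: either the post-hoc step is empty or within-woman correlation is ignored

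*Protocol article*

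**What the plan says.** All places are in the protocol article.

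- Section 2.8.2.2, on the timing of WHOQOL-BREF: "It will be conducted at visits 2, 4, and follow-up". That is three scores per woman.
- Section 2.8.2.1, on skin temperature (ST): readings are taken "at acupoints PC8, LU4, ST32, and LR3 at visit 2, 3, 4, and follow-up". That is four per woman.
- Section 2.4: participants "will be randomly assigned to a UCHA group or a placebo group at a 1:1 ratio". There are two arms.
- Section 2.8.7.1, on the methods for the two secondary outcomes: "a repeated-measure ANOVA for ST and an ANOVA and post-hoc analysis for the WHOQOL-BREF scores".
- The same sentence, on the quantity that these methods compare: "the mean differences in ST and WHOQOL-BREF scores between the groups will be analyzed".
- The same section handles within-group change separately: "the primary and secondary outcome variables will be assessed using a paired *t* test".

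The section does not say whether the WHOQOL-BREF ANOVA takes one value per woman or all three, nor what the post-hoc analysis compares.

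**The concern.** Both secondary outcomes are repeated measurements on the same women. One sentence gives ST a repeated-measures method and WHOQOL-BREF an ordinary ANOVA, without a reason. The post-hoc step makes this more than loose wording. Post-hoc comparisons need a factor with at least three levels, and the treatment factor has two. The natural factor with three levels is visit. With visit as a factor, an ordinary ANOVA uses a single error term for effects that need two different ones. The arm effect is judged against too small an error, and the arm-by-visit effect against too large an error.

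Quality of life is among the items examined in the aim (section 2.1), and the trial is meant to inform a larger one. Two analysts could run materially different tests and both claim to have followed the plan.

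**Working it through.** **Inputs from the article.** Two arms, 1:1 (2.4). WHOQOL-BREF at three visits (2.8.2.2), with visit 2 read as baseline and visit 4 as week 8 from the visit schedule in the text. Significance level 0.05 (2.8.7.1), taken as two-sided. For VAS: difference 10.93, SD 22.28, dropout 20%, 82 per arm (2.8.6).

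**The plan's own figure.** No error rate, power or sample size is given for WHOQOL-BREF. The only figure is the VAS sample size. Assuming 80% power and a two-sided test, neither of which is stated:

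n = 2 × [22.28 × (1.9600 + 0.8416) / 10.93]² = 65.2 per arm; 65.2 / 0.8 = 81.5, rounded up to 82.

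The figure reproduces (rounding to 66 first gives 66 / 0.8 = 82.5, so 83). It does not depend on WHOQOL-BREF and serves here only to set a plausible number of completers, 66 per arm.

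**Assumptions.** Unit variance; equal correlation ρ between any two visits of one woman. The article gives no ρ, so 0.3, 0.5 and 0.7 are used. For power, an assumed benefit of 0.4 SD at both visit 4 and follow-up.

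**Reading A: one value per woman.** With two arms this ANOVA is a two-sample t test. Over 10,000 simulated null trials per ρ, the change score or the 8-week value gave a type I error of 0.049 to 0.052. Nothing is wrong with the arm test. The post-hoc step has no third group to compare. A change to visit 4 omits follow-up, and a change to follow-up omits visit 4.

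**Reading B: all three visits entered as independent rows.** Closed-form checks under the null:

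- Arm effect. The variance of a woman's mean over three visits is (1 + 2ρ)/3, but the test assumes 1/3. False-positive rate = 2 × [1 − Φ(1.96 / √(1 + 2ρ))]. For ρ = 0.5: 1.96 / √2 = 1.386, giving 0.166.
- Arm-by-visit effect. Its true variance is smaller by the factor 1 − ρ. The test therefore rejects when a chi-square on 2 df exceeds 5.99 / (1 − ρ), which has probability 0.05^(1/(1−ρ)). For ρ = 0.5: 0.05² = 0.0025.

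| Quantity | ρ = 0.3 | ρ = 0.5 | ρ = 0.7 |
|---|---|---|---|
| Arm effect, null, formula | 0.121 | 0.166 | 0.206 |
| Arm effect, null, simulated | 0.121 | 0.162 | 0.209 |
| Arm-by-visit, null, formula | 0.014 | 0.0025 | 0.00005 |
| Arm-by-visit, null, simulated | 0.014 | 0.002 | 0.000 |
| Arm-by-visit power, ordinary ANOVA | 0.31 | 0.26 | 0.19 |
| Arm-by-visit power, repeated measures | 0.49 | 0.65 | 0.87 |
| Change-score ANOVA power at visit 4 (reading A) | 0.49 | 0.62 | 0.84 |

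Repeated-measures ANOVA on the same simulated data held 0.046 to 0.053 for both effects.

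**Sensitivity.** A separate simulation (6,000 trials, 65 per arm, 0.5 SD benefit) gave arm-effect error of 12.0%, 16.6% and 20.4%, and arm-by-visit error of 1.5%, 0.3% and 0.0%. At ρ = 0.5, arm-by-visit power was 48% against 84% with repeated measures. With all 82 per arm and ρ = 0.5, the arm-effect error was 16.0%, and power was 64% against 92%.

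**The case against.** The strongest case against is that the article never says visits are pooled. It speaks of mean differences between the groups, which suits one change per woman. The same section uses plain ANOVA to compare baseline continuous variables between the two arms, which is one value per woman, and it writes repeated-measure ANOVA where it means that. The schedule also suggests a reason for the difference: WHOQOL-BREF skips visit 3, and for the primary outcome the section says "The between-groups analysis after 8 weeks of administration will be performed". On that window WHOQOL-BREF has a single before-and-after pair. The post-hoc phrase may simply be surplus, since the same paragraph names an SDT group that this trial does not have. Finally, the inflated arm main effect averages in the baseline visit, so it is not the difference in change that matters most.

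Much of this stands. A reader might infer that the planned quality-of-life error rates are wrong. The documents do not support that, because reading A is open, is valid, and at 8 weeks costs 0 to 3 points of power against repeated measures (0.49, 0.62, 0.84 against 0.49, 0.65, 0.87).

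Two things remain. First, the post-hoc step is attached to WHOQOL-BREF and not to the baseline ANOVA, so the baseline usage does not explain it. Hospital would supply enough levels, but the section names no such factor. The five WHOQOL-BREF domains are themselves within-woman and would raise the same independence problem. Second, factors and time points that a condensed article leaves to the full protocol would not be a finding, but here a method is stated, and the stated step does not fit the stated design.

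**Conclusion.** The point holds in conditional form. With two arms and three visits, the stated WHOQOL-BREF analysis is either a valid arm test with an empty post-hoc step that leaves out a visit, or an ordinary ANOVA that ignores within-woman correlation. Only the second does harm: about 12% to 21% false positives for the arm effect, and an arm-by-visit test that rejects in about 1.5% of null trials or fewer and loses power. These sizes rest on equal correlations of 0.3 to 0.7, 65 or 66 completers per arm, and assumed benefits of 0.4 or 0.5 SD, none of which the article gives for WHOQOL-BREF. WHOQOL-BREF is a secondary outcome in an exploratory trial. The VAS result and the sample size of 82 per arm do not depend on it.

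**What to change.** In section 2.8.7.1, replace the WHOQOL-BREF phrase with a repeated-measures (or mixed) model for each domain, with arm, visit and arm-by-visit as terms and participant as the repeated unit. Report the UCHA-minus-placebo difference in change at visit 4 and at follow-up with 95% CIs, and delete the post-hoc step. This matches the approach already chosen for ST, brings follow-up into the test and closes off the invalid reading.

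An acceptable minimum is one named change score per woman, compared by ANOVA or by baseline-adjusted ANCOVA, with no post-hoc step.

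The cost is one sentence and slightly more analysis work. No additional data are needed, and the planned SPSS version can fit the model.

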##### Safety assessment

2.8.7.2

Safety analysis will be conducted for all subjects who will be randomized and would visit at least once after screening. Safety-related measures will be analyzed using the ITT method. The safety data will be stratified according to the symptoms.

### Data management and monitoring

2.9

All records will be collected in paper CRF documents. To protect personal confidentiality, the files would be stored in a secure and locked place without any personally identifiable information. After trial completion, 2 independent technicians will perform data entry for promoting the data quality. After finishing the data entry and dealing with the queries by range checking, the database will be locked and analyzed by independent professional statistician of ISEE. Site PIs will have direct access to the final data sets from their own sites. Monitoring will be performed by ISEE and will begin after the first participant completes the entire course of the study. All institutions conducting trials will be monitored in accordance with the SOPs during the trial. No auditing will be performed for this trial.

### Ethics approval and consent to participate

2.10

This trial has been approved by the IRBs of five hospitals (Gachon University Gil Korean Medical Hospital: 18–102, Kyung Hee University Oriental Medical Center: KOMCIRB-2018–09–006, Kyung Hee University Korean Medicine Hospital at Gangdong: KHNMCOH2018-09-001, Korean Medical Hospital of Sangji University: SJIRB-18-003 and Semyung University Second Affiliated Korean Medical Hospital at Chungju: SMCJH 1810-06). The trial will be conducted in accordance with the Helsinki declaration and the Good Clinical Practice Guidelines of the Korea Food and Drug Administration. All participants will be signed the written informed consent document and received the copied consent documents prior to any trial procedures.

If any protocol changes which may have impacted the trial, it must approve by the site IRB prior to implementation. After approval, each site PI should be notified and trained the site staffs before initiating the trial.

The results of this UCHA trial will be disseminated through scientific journals or poster presentations at medical conferences. The public access to any trial data set is still unplanned.

## Discussion

3

This pilot study is aimed to explore the clinical efficacy and safety of UCHA to treat CHHF patients. Recently, CHHF has been observed to affect the quality of daily life of individuals in East Asian countries, which can be considered as the women's burden of disease. In Korean medicine, CHHF has been known as a cold-related symptom and pattern, which requires careful attention to prevent symptom worsening and further pattern progression into a severe concomitant illness. Traditional herbal medicine is commonly used in the treatment of CHHF in Korea. However, the evidence of efficacy and safety is not investigated rigorously. Therefore, the establishment of systemic treatment option as well as its guideline for CHHF is essential.

This trial is the first well-designed RCT to evaluate the efficacy and safety of UCHA compared to placebo in patients with CHHF in Korea, which is the major strength of this study. However, this trial has several limitations. First, due to the diversity in IP manufacturing companies, IPs cannot be manufactured with a remarkably same appearance with each other. To minimize the unblinding, we make the samples several times to develop a placebo that cannot be noticed by patients by arranging researcher meetings. The second is the limited use of scientific quantitative outcome measurements. In Western medicine, the assessment of cold intolerance-related diseases typically involves infrared thermography, cold stress test (CST), and heart rate variability analysis to quantify the severity of the disease. However, previously, our team performed a study^[17]^ on CHHF with herbal medicine, Danggui-SayukGa-Osuyu-Saenggang-tang, and conducted the CST, which is a more accurate measuring method to establish the efficacy of herbal medicine on CHHF. However, the study did not reveal any significant difference on groups after treatment and it had a higher risk of assessment bias during the performing test; we, therefore, had to exclude it from the outcome measurement.

Despite these limitations, as the first trial to examine the efficacy and safety of UCHA on CHHF patients, we expect that the study findings may provide informative evidence to design a confirmative, large-scale RCT in the near future. Moreover, it will help practitioners to utilize UCHA as a therapeutic regimen for CHHF.

### Trial status

3.1

Participant recruitment has begun on January 31, 2019, and 72 participants have been recruited until now. And it will complete in May 2020.
